### Participants

Study participants are comprised of [1] community health-care providers and [2] pregnant women with OUD. Community health-care providers include nurse practitioners, physician’s assistants, obstetricians, pediatricians, family practice physicians, behavioral health care professionals, and child protective services caseworkers practicing within the targeted counties who are willing to participate in the educational sessions delivered by the project team and provide informed consent.

Pregnant women with OUD participants include those who are living in the targeted counties, who are not currently incarcerated, and who provide informed consent. During the intervention phase, women are encouraged to engage in in physical, mental, or behavioral health service by the project nurse care manager that is congruent with the participants needs for prenatal care, OUD recovery, and wellness for mother and fetus. These participants are being recruited with the help of the community-based nurse care manager through posting fliers and communicating directly with potential referral sources, such as local healthcare providers, local health department, and the division of child and family services. The nurse care manager also obtains informed consent. Although the study sample is not powered a priori to achieve a pre-specific treatment effect, a nurse care manager who is well integrated in the local community is part of the research team and leverages relationships with local referral sources to achieve adequate participant enrollment. The nurse care manager obtains locator information for each enrolled participant, and continues checking in with participants to ensure retention and follow-up. The research team meets weekly with the nurse care manager to ensure several follow-up attempts are made for purposes of enrolling and collecting data from participants.

### Needs assessment and implementation evaluation

The CFIR and RE-AIM models are being used in complement to one another to guide and evaluate implementation of this project. The CFIR is used in this study to assess contextual factors influencing implementation in the needs assessment and throughout study duration to assess continued needs and any changes across time related to the project interventions [26]. The RE-AIM model is applied to efficiently and comprehensively evaluate implementation outcomes of the multilevel intervention at the end of the study [27].

Prior to the implementation of the educational intervention, the research team conducted a community needs assessment. This was done in order to measure CFIR constructs that may influence implementation success (Table 1), and included healthcare provider, community representative, and patient advocate assessments (see Additional file 1: Figs. S1–3). Likewise, this study also includes assessments at these three levels at the study midpoint and following study conclusion, which have yet to be completed in real-time. In real-time, pre-implementation components of this project have been completed. Data collection at the patient-level begins when participants enroll in the study and continues through the end of their study participation. At study conclusion, RE-AIM measures of implementation success are evaluated (Table 2). Finally, analyses occur at the conclusion of the study after patient enrollment has ended.

#### Windshield survey

The pre-implementation needs assessment also included a windshield survey to help researchers gain an understanding of the community characteristics [35]. Windshield surveys involve surveying an area of interest by foot or in a vehicle and recording observations related to community safety, resources, barriers, and accessibility of care. This project component followed a standardized guide adapted from Callan, [35] wherein trained research assistants drove within areas of the targeted counties where health care services are primarily located to assess clinic/agency availability, location and distance, physical accessibility (sidewalks, bus stops), and presentation (graffiti, general appearance, disrepair). Results of the windshield survey allowed our team to identify service gaps and needs within the targeted communities and surrounding areas.

#### Provider assessments

Provider assessments occur at three distinct time-points: pre-implementation (immediately preceding the kick-off event), mid-implementation (3 monthspost-kick-offevent), and post-implementation (final month of the project) (see Table 3). Qualitative interview questions were adapted from the CFIR Interview Guide Tool [36]. In the pre-implementation phase, these interviews informed our needs assessment, and discussed barriers and facilitators with retention of women with OUD in obstetric and OUD care and provider skills and knowledge in training topic areas. In the mid- and post-implementation phases, qualitative items were modified to assess any improvements related to the intervention implementation as well as provider satisfaction with support/education (see Table 2).

**Table 3 Tab3:** Provider-Level Study Measures

Outcome	Level	Domain	Instrument	Source	Pre-Implementation (Time 1)	Mid-Implementation (Time 2)	Post-Implementation (Time 3)
Patient retention in care	Provider	QI	# patients treated/provider	Self-report	X	X	X
Pre-/Post-learning knowledge & skills (physical health)	Provider	QI	Mixed methods survey	Self-report	X		
Pre-/Post-learning knowledge & skills (mental health)	Provider	QI	Mixed methods survey	Self-report	X		
Provider satisfaction with support	Provider	QI	Mixed methods survey; quantitative interview	Self-report	X	X	X
Provider attitudes and perceptions towards substance misuse	Provider	QI	SAP-1; AAPPQ/adapted AAPPQ	Self-report	X	X	X
Acceptability of intervention	Provider	QI	EBPAS	Self-report	X	X	X
Perception of improvement in care for pregnant women with OUD in community	Provider	QI	Mixed methods survey; quantitative interview	Self-report			X
Program Maintenance	Provider	QI	Mixed methods survey; quantitative interview	Self-report			X
Adoption of evidence-based practices	Provider	QI	Mixed methods surveys; quantitative interview	Self-report		X	X

SAP-1 SBIRT Attitudes & Perceptions, *AAPPQ* Alcohol & Alcohol Problems Perceptions Questionnaire, *EBPAS* Evidence-Based Practices and Attitudes Scale

Assessments also included self-report quantitative assessments administered via web-based survey. Pre-implementation quantitative surveys also helped to inform our needs assessment. These surveys were adapted from the Evidence-Based Practices and Attitudes Scale (EBPAS) which assesses provider attitudes and perceptions towards adopting new interventions, [37] and the SBIRT Attitudes and Perceptions (SAP-1) Questionnaire which assesses substance use screening, intervention, and referral services competency [38]. Additionally, the Alcohol and Alcohol Problems Perceptions Questionnaire (AAPPQ) was utilized and adapted for opioid use to assess provider attitudes towards serving individuals with substance use [39]. In the mid- and post-implementation phases, quantitative items were repeated in a modified form to assess any improvements related to the intervention implementation. In addition, providers participated in the baseline kick off training which included a webinar on perinatal OUD treatment and NOWS presented by research team physicians. Attendees completed learning assessments related to the training sessions and subsequent satisfaction.

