### Barriers to implementation in rural areas

Rates of maternal opioid use and NOWS in rural areas have climbed substantially over the past ten years compared to their urban counterparts [16], yet treatment engagement among this population has failed to keep pace [17], While the effectiveness of MOUD in treating OUD is well-established, [13] the limited availability of buprenorphine (BUP) prescribers and methadone clinics in rural areas has created a substantial barrier to accessing these life-saving treatments for those with OUD—including pregnant women [18, 19]. Within rural areas, buprenorphine prescribers frequently do not treat pregnant patients [20]. Indeed, mothers with OUD and their infants living in rural areas frequently require transfer to other hospitals following delivery to receive high-level, specialty substance use and neonatal care [21]. Perceptions of OUD as a moral failing among pregnant women have given rise to punitive approaches rather than evidence-based medical care [22]. Rural prescribers also identify stigma from other providers as a major barrier to providing MOUD [23]. Lack of specialty support for complex problems, such as perinatal OUD, also creates a significant barrier to rural healthcare providers offering MOUD [24]. As of 2017, 60.1% of rural counties did not have a buprenorphine-waivered physician [25].

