To what extent did perinatal addiction education reach the pregnant women with OUD within the healthcare system in Your Counties?	Local healthcare and social service agencies	Electronic medical records; health department records	Number of patient participants/ total number of pregnant women with opioid misuse in Your Counties during the study duration
Efficacy			
How effective was the provider training and support?	Community providers	Questionnaires assessing skills, knowledge and satisfaction	Mixed method surveys regarding provider experience and skillset
How effective were perinatal addiction education services in improving care for pregnant women with OUD?	Healthcare and social service records; patient participants	Compare data regarding illicit substance use, MOUD continuity, opioid poisoning occurrences, physical and mental health, and social service involvement; questionnaires to assess patient perception	Medical codes; standardized comprehensive wellness measurement instruments; qualitative surveys
Adoption			
To what extent are community providers using perinatal addiction education practices when treating patients with perinatal OUD?	Community providers; local healthcare agencies	Questionnaires assessing provider practices and attitudes; electronic medical records	Mixed methods surveys regarding provider practices; frequency of MOUD provision, NOWS treatment and SBIRT by participating community providers
To what extent are patients utilizing resources made available through the perinatal addiction education program?	Partnering agencies (e.g. EUWH, Four Corners Behavioral Health); medical records; pharmacy records	Interviews with partner agencies; electronic medical record and pharmacy record evaluation	Utilization of care management and resources made available through this project; number of MOUD prescriptions filled; presence of BUP in urinalysis via medical record
Implementation			
What were the barriers and facilitators of high quality care?	Community providers	Questionnaires and focus groups	Perceptions of and feedback regarding the implementation kickoff event, as well as ongoing training and support provided via the implementation of perinatal addiction education
Maintenance			

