	Neonatal opioid withdrawal syndrome (NOWS) severity	Health	ICD10 Code P96.1	Medical record			X
	Length of hospital stay	Health	Discharge dates	Medical record			X
	Continuity of MOUD	QI	Prescriptions Filled	Medical record			X
	Illicit drug use	SUD	Urinalysis	Medical record	X	X	X
	Number of infant ER visits	Health	CPT 99,281–99,285	Medical record			X
	Adequacy of prenatal care	QI	Adequacy of Prenatal Care Utilization (APNCU)	Calculated from medical record			X
Medical record/self-report	Overdose events	SUD	ICD10 Code T40.2X1A	Medical record/Self-report	X		X
Self-report	Overall health	All	12-Item Short Form Survey (SF-12)	Self-report	X	X	X
	Substance misuse	SUD	Adapted Drug Abuse Screening Test (DAST)	Self-report	X	X	X
	Trauma history	Social	Adverse Childhood Experience (ACE)	Self-report	X		
	Alcohol misuse	SUD	Alcohol Use Disorders Identification-Concise (AUDIT-C)	Self-report	X	X	X
	OUD	SUD	Diagnostic and Statistical Manual 5 (DSM-5) Opioid Use Disorder (OUD) Checklist	Self-report	X	X	X
	Depression	Mental Health	Edinburgh Postnatal Depression Scale (EPDS), Patient Health Questionnaire-9 (PHQ-9)	Self-report	X	X	X
	Nicotine dependence	SUD	Fagerstrom Test for Nicotine Dependence (FTND)	Self-report	X	X	X
	Anxiety	Mental health	Generalized Anxiety Disorder-7 (GAD-7)	Self-report	X	X	X
	Psychological distress	Mental health	Kessler Psychological Distress Scale (K6)	Self-report	X	X	X
	Parental knowledge & skills	Social	Parenting and Family Adjustment Scale (PAFAS)	Self-report	X		X
	Patient satisfaction	QI	Patient Satisfaction Questionnaire Short Form (PSQ-18)	Self-report		X	X
	Patient utilization of services	QI	Treatment Services Review-6 (TSR-6)	Self-report	X	X	X
	Post-traumatic stress disorder (PTSD)	Mental health	Primary Care PTSD Screen for DSM-5 (PC-PTSD-5)	Self-report	X	X	X

*QI* quality improvement, *SUD* Substance Use Disorder, *IC10* International Classification of Disease, 10th Revision, *CPT* Current Procedural Terminology

Our team chose several reliable and valid self-report instruments to assess substance use at the patient-level. The Alcohol Use Disorders Identification-Concise (AUDIT-C) is a measure of unhealthy alcohol use [40]. The Diagnostic and Statistical Manual 5 (DSM-5) OUD Checklist is an instrument to assess OUD [41]. The Fagerstrom Test for Nicotine Dependence (FTND) captures the presence of nicotine dependence [42]. Finally, we adapted the Drug Abuse Screening Test (DAST) [43] to assess opioid-specific participant behaviors.

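### Table 3 measures retention in care by provider caseload, and Table 4 measures MOUD continuity by prescriptions filled at one time point, with no baseline and no stated denominator

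*Protocol article*

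**What the plan says.** **Retention.** Table 3 (Provider assessments) lists "Patient retention in care" as a provider-level quality-improvement outcome. Its instrument is the number of "patients treated/provider", by self-report, at all three provider time points: "pre-implementation (immediately preceding the kick-off event), mid-implementation (3 monthspost-kick-offevent), and post-implementation (final month of the project").

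**MOUD continuity.** Table 4 (Participant assessments) lists continuity of MOUD with the instrument "Prescriptions Filled", taken from the medical record and marked only in the post-delivery column. Table 2 (Implementation framework) touches on it twice. Under Efficacy the method begins "Compare data regarding illicit substance use, MOUD continuity, opioid poisoning occurrences". Under Adoption the measures include "number of MOUD prescriptions filled; presence of BUP in urinalysis via medical record".

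**Follow-up.** "Data collection at the patient-level begins when participants enroll in the study and continues through the end of their study participation" (Needs assessment and implementation evaluation). The Participants section gives no gestational-age window for enrolment. The last assessment is 30 days after delivery, and data collection stops if a woman withdraws.

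**Aim and analysis.** Treatment engagement is one of two patient-level targets named under Design. The same section says that the team wants to assess change over time and that the study has a single arm. Analyses plans t-tests and chi-square tests, cross-sectionally and across time points, with no subgroup analyses.

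**The concern.** Retention is a property of women who have started care: of those who entered, how many are still there. A provider's count of patients treated has no such denominator. A woman seen once counts the same as one kept throughout. The programme works to increase referrals and trains providers in referral, so success at referral would raise the count whether or not women stay. A reader of the results could take a larger caseload for better retention.

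MOUD continuity has a different weakness. In a single-arm study interested in change, one time point offers nothing to compare with. A number of fills also accumulates over follow-up, and follow-up length is set by the gestational age at which a woman happens to enrol. Early and late enrollers with the same adherence would then receive different values.

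**Working it through.** The article states no sample size, power or effect for these outcomes, so there is no figure to reproduce. The check sets the instruments against the constructs and then illustrates the size.

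**1. Caseload against retention.** Women retained = women treated × proportion retained. The inputs are illustrative.

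| Treated | Retained (%) | Women retained | Table 3 measure |
|---|---|---|---|
| 4 | 100 | 4 | 4 |
| 8 | 50 | 4 | 8 |
| 16 | 25 | 4 | 16 |

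The measure quadruples while retention falls from 100% to 25% and the number of women kept in care does not change.

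**2. Is there a baseline for MOUD continuity?** Table 4 marks one column, post-delivery. It does mark baseline for another medical-record item, urinalysis for illicit drug use, which has all three columns. So the table shows baseline record data where they are intended. A single late extraction could look back over pregnancy, but patient-level collection is said to start at enrolment, so nothing stated supplies a pre-enrolment value. No comparison group is described. The county-level data to be obtained from local health officials cover infections, overdoses and child welfare, not MOUD continuity.

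**3. How a fill count depends on enrolment time.** Follow-up days = (delivery week − enrolment week) × 7 + 30. The 30 days come from the article. Delivery week, enrolment week and days per fill are assumptions. Whole fills at perfect continuity = days ÷ days per fill, rounded up. With delivery at 39 weeks:

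| Enrolment week | Follow-up days | 28-day fills | 7-day fills |
|---|---|---|---|
| 8 | 31 × 7 + 30 = 247 | 9 | 36 |
| 12 | 27 × 7 + 30 = 219 | 8 | 32 |
| 20 | 19 × 7 + 30 = 163 | 6 | 24 |
| 28 | 11 × 7 + 30 = 107 | 4 | 16 |
| 34 | 5 × 7 + 30 = 65 | 3 | 10 |

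Ratio of follow-up, 12 against 28 weeks: 219 ÷ 107 = 2.05. For 8 against 34 weeks: 247 ÷ 65 = 3.8. In whole fills, the 8-against-34 ratio is 9 ÷ 3 = 3.0 for 28-day supplies and 36 ÷ 10 = 3.6 for 7-day supplies. With delivery at 37 weeks the follow-up ratios are 205 ÷ 93 = 2.2 and 233 ÷ 51 = 4.6. Prescription length alone changes the count about fourfold (36 against 9).

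**4. The same count, read as days covered.** Four 28-day fills supply 112 days. With delivery at 39 weeks, that covers 112 ÷ 219 = 51% of follow-up for a woman enrolled at 12 weeks, 112 ÷ 163 = 69% at 20 weeks, and all 107 days at 28 weeks.

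**The case against.** **Other measures of engagement exist.** The TSR-6 is collected at baseline, pre-delivery and post-delivery. The APNCU index, buprenorphine in urine and a weekly care management form add to it. This stands. A reader might infer that treatment engagement is unmeasured or has no baseline at all, and the article does not support that. But the TSR-6 is general self-reported service use and the APNCU concerns prenatal care after the fact. Neither turns caseload into retention or gives MOUD continuity a baseline.

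**Retention is a provider-level item.** It sits in the provider table as quality improvement, so the error does not by itself undermine the patient-level aim. This stands as a limit on reach. The label and instrument still disagree.

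**Continuity is not said to be a raw count.** Table 4 does not specify a total. The word for number appears under Adoption, while continuity appears under Efficacy. A days-covered definition could be in the full protocol. This is fair, and the dependence on enrolment time is therefore conditional on analysis as a count. The single marked time point is stated in the article.

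**Comparison need not mean before and after.** Table 2 does not say what is compared, so this is a gap to resolve rather than a proven contradiction. With no control group and no subgroup analyses, though, change over time is the only evident candidate.

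**Two further inferences fail.** Dependence on each woman's follow-up and the single post-delivery mark do not apply to the provider count, which is taken at three times. Nor can one conclude that women on methadone would be scored as untreated. The article mentions "the limited availability of buprenorphine (BUP) prescribers and methadone clinics in rural areas" as a barrier, but does not say how methadone is dispensed or recorded, or that any participant receives it.

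**Conclusion.** The concern holds for two named outcomes. Table 3's retention instrument is caseload and can move opposite to retention. This follows from the stated instrument and needs no assumption. MOUD continuity is marked at one time point, so the schedule provides no before/after comparison. If it is analysed as a count, it varies with enrolment timing at identical continuity: about 2-fold for enrolment at 12 against 28 weeks, and up to about 3.8-fold at the extremes of 8 against 34 weeks, assuming delivery at 39 weeks. The direction does not depend on those assumptions, but the size does. Fills remain a partial proxy for MOUD uptake, so it would be too strong to say that they carry no information on engagement. Pilot status excuses the lack of a powered analysis, but not an outcome whose label and instrument differ. The change should be made before the end-of-study analysis.

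**What to change.** 1. Keep the provider count in Table 3, relabel it as caseload, and draw no conclusion on retention from it.
2. Define retention as the number of women still in prenatal or MOUD care at each follow-up divided by all women enrolled, using the records and TSR-6 already collected. State how women who withdraw are counted, since their data collection stops.
3. Express MOUD continuity as days covered ÷ each woman's own days from enrolment to 30 days after delivery.
4. Compute the same proportion over a fixed look-back before enrolment (for example 90 days) as the baseline, mark it in Table 4, and state in Table 2 that this is the comparison intended.

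The cost is slightly more record abstraction: fill dates, days supplied and the look-back period. No new visits are needed. The before/after comparison would still be uncontrolled, as the single-arm design implies.

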## Methods

### Design

This two-year study is employing a one group, repeated measures, hybrid type-1 effectiveness-implementation design, [28] which emphasizes clinical effectiveness monitoring while also gathering information regarding the implementation of the program. This study delivers interventions at 2 levels, both targeting improvement of care for pregnant women with OUD. The first area of focus is at the *community healthcare provider-level*, which aims to evaluate the acceptability and feasibility of perinatal OUD education across time and to improve provider education by increasing knowledge specific to: MOUD provision; screening, brief intervention, and referral to treatment (SBIRT) utilization; and NOWS treatment. The second area of intervention focus is at the *patient-level*, which assesses the preliminary effect of perinatal OUD provider education in promoting illicit opioid abstinence and treatment engagement among pregnant women with OUD. The research team is interested in assessing changes across time among recipients. Time and resources necessary to implement an experimental or quasi-experimental design are not available for this project. For this reason, the research team has chosen to utilize a single arm design. The University of Utah Institutional Review Board approved this study.

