### Analyses

Following study conclusion, we will employ descriptive statistics to calculate measures of central tendency, frequencies, and proportions for patient demographics and substance use, health, social, and mother/child indicators.* T*-tests and* χ*^2^ tests will be used to assess mean and proportional differences in both cross-sectional and changes in repeated measures across study time points for participant outcomes. As this is a pilot study, powered analyses are not the purpose of this project and thus we do not have a target number of participants for enrollment [55]. The research team will not be conducting subgroup or interim analyses.

Qualitative data collected during the community needs assessment will be analyzed using the procedure for Rapid Identification of Themes from Audio Recordings (RITA) described by Neal and colleagues [56]. Though the inclusion of qualitative data can greatly enrich quantitative data, the slow and labor-intensive process of analyzing it can be a barrier due to time constraints [57, 58]. The RITA approach was developed as way to increase the speed of the analysis process while preserving more of the original data. It is applied to the actual audio recordings of semi-structured interviews. The process involves several time-saving steps to improve efficiency of qualitative data analysis. These include pinpointing research foci for which RITA will be used, creating a codebook of key themes identified and their valence (positive, neutral, or negative context), creating a coding form, refining the codebook, coding, and analyzing codes. A key time-saving feature of RITA is that during analysis, audio recordings are broken down into shorter time segments. The coding form is a grid listing themes and time segments, and coders mark the themes present in each time segment [56].

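### Provider survey items are modified after baseline but scheduled as one repeated measure, so change from Time 1 may partly reflect the change of instrument

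*Protocol article*

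**What the plan says.** The Provider assessments section sets three occasions: before implementation (just ahead of the kick-off event), three months after kick-off, and the final month of the project. The web-based quantitative surveys draw on three instruments. For EBPAS and SAP-1 the article says "These surveys were adapted from the Evidence-Based Practices and Attitudes Scale (EBPAS) which assesses provider attitudes and perceptions towards adopting new interventions", and it then adds SAP-1 for screening and referral competency. The AAPPQ "was utilized and adapted for opioid use to assess provider attitudes towards serving individuals with substance use". On the later occasions, "In the mid- and post-implementation phases, quantitative items were repeated in a modified form to assess any improvements related to the intervention implementation".

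Table 3 marks provider attitudes ("SAP-1; AAPPQ/adapted AAPPQ") and acceptability of the intervention (EBPAS) at all three times. It does not say which version is used when.

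Change over time is a stated purpose. The Design section says the provider-level work "aims to evaluate the acceptability and feasibility of perinatal OUD education across time". The Analyses section says that t-tests and chi-square tests "will be used to assess mean and proportional differences in both cross-sectional and changes in repeated measures across study time points for participant outcomes". The Participants section counts providers among the study participants. Design and Limitations both describe a single arm, and Limitations states that there is no control group.

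**The concern.** A pre-post score difference measures change in providers only if the same items, with the same response options and scoring, are used on both occasions. Here the article says the items were modified after baseline, and the switch falls exactly between pre and post. Every provider moves from the Time 1 form to the later form, and no concurrent group answers the later form without the intervention. A shift caused by the form therefore looks the same as a shift caused by the education programme.

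At stake is the reading of the attitude and acceptability scales as evidence that provider education worked. Table 2 uses provider questionnaires for both the Efficacy and Adoption dimensions of RE-AIM.

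**Working it through.** **Passages side by side.**

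| Place in the protocol article | What it implies |
|---|---|
| Provider assessments, text | Quantitative items repeated at mid- and post-implementation, in modified form, to assess improvement |
| Table 3 | SAP-1, AAPPQ/adapted AAPPQ and EBPAS marked at Times 1, 2 and 3, with no version stated |
| Design; Limitations | One group, no control |
| Participant assessments (patients) | Follow-ups keep the baseline questionnaires, except the ACE scale, for which a reason is given |

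The sentence on quantitative items cannot be read as referring to the interviews alone, because the article says separately that the qualitative items were modified. No unmodified core set, anchor items or bridging step is described for the provider scales. At the patient level the same questionnaires are retained.

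**What the contrast estimates.** Let τ be the true mean change in providers and β the mean score shift caused by the change of items alone. Then:

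- Expected (Time 2 − Time 1) = τ + β, and likewise for Time 3 − Time 1 with that form's own β.
- With one group, only the sum τ + β can be estimated.
- The standard error of the mean change is σ_D/√n, where σ_D is the SD of the paired change. It falls as n grows; β does not.
- Time 3 − Time 2 is affected only if the two later forms also differ from each other, which the article does not say.
- Adapting a scale before Time 1, such as AAPPQ from alcohol to opioids, does not bias change if that adapted version is then held fixed.

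**Illustration of size.** The article gives no number of providers, SD, alpha or expected shift, so there is no figure of its own to reproduce. All inputs below are assumptions: τ = 0, a two-sided 5% paired t-test, b = β/σ_D, and n providers with paired data.

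Non-centrality = b√n. Rejection probability = 1 − F(c) + F(−c), where F is the non-central t distribution function on n − 1 degrees of freedom and c is the 97.5% point of the central t.

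Example: n = 20 and b = 0.3 give non-centrality 0.3 × √20 = 1.34 and a rejection probability of 0.247.

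| Assumed shift b | n = 10 | n = 20 | n = 40 |
|---|---|---|---|
| 0 | 5.0% | 5.0% | 5.0% |
| 0.2 | 8.8% | 13.6% | 23.5% |
| 0.3 | 13.6% | 24.7% | 45.7% |
| 0.5 | 29.3% | 56.5% | 86.9% |

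The test is two-sided, so a shift in either direction gives the same rates. The table shows that a fixed artefact does more damage as n rises. It does not show that an artefact of any given size exists here.

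**The case against.** Several points on the other side are sound.

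- **The modification is not described.** A reader might infer that the items were reworded. The article says only that they took a modified form, which could mean added or dropped items, a changed stem or tense, or rewording. If items were only added or dropped, the common items stay comparable, though total scores may not. The pre-implementation assessment forms are in an additional file that is not shown.
- **Direction is unknown.** A reader might infer that items were rewritten to pick up improvement and so would push scores upward. The purpose clause can as well attach to the repetition: the items were asked again in order to assess improvement. No direction of bias follows.
- **No test is named for the provider scales.** The Analyses paragraph opens with patient indicators and then refers to participant outcomes. Providers are called participants elsewhere, so the paired t-test is a possible reading but an inferred one.
- **The Table 3 entry is weak support.** "SAP-1; AAPPQ/adapted AAPPQ" most likely reflects the opioid adaptation and not a switch between times.
- **This is a pilot.** It has no powered analyses and no enrolment target. The Discussion places the effectiveness question at the patient level, and providers are also assessed by interviews and by satisfaction and adoption measures.

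These points limit the strength of the finding but do not remove it. Pilot status excuses imprecision, not a change score whose two ends come from different forms. Nor can a later analysis plan recover comparability for items that were not asked the same way twice. The stated aim of assessing improvement makes the pre-post comparison a purpose of the surveys, whichever test is used.

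**Conclusion.** The point holds in a limited form. The article says scored provider items were modified after Time 1, while Table 3 treats the scales as constant. To the extent that those items differ, the pre-to-mid and pre-to-post differences confound instrument with provider change, and the one-group design offers no way to separate them. The size and direction of the bias cannot be determined from the document, and the rejection rates above are illustrations under assumed inputs. Severity is moderate: the scales are provider-level measures in an unpowered pilot, and no patient-level questionnaire is affected. Confidence is moderate too, because the extent of the modification is not visible.

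**What to change.** 1. At Times 2 and 3, administer the Time 1 items (in their already adapted form) unchanged, with the same response scales and scoring.
2. Put new or modified intervention-specific items in a separate block after the core items, and exclude them from change scores.
3. State in Table 3 which version of EBPAS, SAP-1 and AAPPQ is used at each time.
4. If a modified survey has already been fielded, limit change analyses to items identical at all times, and report modified items only descriptively at the time they were asked.

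The cost is a web-survey edit and a slightly longer questionnaire or, under step 4, fewer items in the change score and a departure from the scales' full scoring. There may still be time: the Needs assessment and implementation evaluation section says the midpoint and final assessments were still to be completed, although the past tense in the Provider assessments section leaves that uncertain. The sponsor should confirm which forms have gone out.
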